**Version 4. Clean Date: September 18,2024**

| Table 1. Father Recruitment Criteria                                                                                            |   |
|---------------------------------------------------------------------------------------------------------------------------------|---|
| Inclusion Criteria                                                                                                              |   |
| Live with and be responsible for the care of at least one child aged 8-17 years                                                 |   |
| 18 to 65 years of age                                                                                                           |   |
| Elevated depression symptoms (PHQ-9 > 5)                                                                           |   |
| Any alcohol use (AUDIT>0)                                                                                                       |   |
| Child at risk of MH problems (SDQ > 13)                                                                            |   |
| Willingness for family member to participate                                                                                    |   |
| Exclusion Criteria                                                                                                              |   |
| Severe depression symptoms (PHQ-9 > 19)                                                                                         |   |
| Severe risk/likely alcohol dependence that warrants medical management (AUDIT > 20)                                |   |
| Severe risk/likely substance use dependence that warrants medical management (‘yes’ score in two or more questions in CAGE-AID) |   |
| Violent legal offences                                                                                                          | 2 |
| Any indicator of severe violence (CTS items)                                                                                    |   |
| Inability to provide informed consent, and/or complete procedures in Swahili or English (orally).                               |   |

referrals to care in the area to all individuals who report problems or referrals to higher levels of care to those who need it. Referral will continue to include the community substance use groups run by MTRH when appropriate. Consenters will complete the consent process and conduct the eligibility screening first with the father and then with other family members when the father is eligible. Eligibility and screening will occur first with fathers, then co-caregivers, then the target child. The target child will be chosen based on age first, then highest SDQ score based on caregiver screeners. *All individuals who report symptoms will be referred to care as usual.*

**Consenting and Safety Considerations:** The study will follow WHO guidelines on conducting research with individuals who may be at risk of violence as a precaution. Guidelines will inform consent forms, procedures, and personnel training. Procedures are detailed in Human Subjects 3.1. Briefly, with fathers, **trained consenters** (i.e., the study RA and PC and or other trained medical psychologists) will assess interest, complete consent, and conduct eligibility screening. Study inclusion/exclusion will be explained in general terms to not place any youth or co-caregivers at risk later if a family is ineligible. Scripts will be developed with our community partners. Fathers excluded due to severe symptomology or severe violence will be referred to a higher level of care within MTRH (Human Subjects 3.1). The CHW will ask eligible fathers for permission to invite a co-caregiver to answer screening questions about the child, emphasizing that all information beyond basic study detail will be kept private from the co-caregiver and vice versa (a process used in the proof-of-concept pilot). The co-caregiver will then be consented and screened in a private location (SDQ; CTS); if the CTS indicates presence or likelihood of severe violence, a safety assessment will be conducted and referrals provided while respecting women's autonomy. Fathers' ineligible in this scenario will be revisited later by the CHW, asked dummy questions, and told they are ineligible using non-descript language; referrals and an appointment to care will be provided to MTRH. If the father is eligible after both screenings, the target child will complete assent and a brief screen (SDQ). **Recruitment feasibility:** Based on ongoing studies, we estimate recruiting 2-4 fathers per week. This rate will allow us to recruit 102 families within 24 months.

**Peer-father counselor recruitment, training, supervision.** To recruit, select, supervise, and train peer-father counselors, we will use approaches employed in our preliminary pilot that

demonstrated feasibility. **Recruitment and selection:** We will recruit 12 peer-fathers through community leaders (e.g., religious leaders, chiefs, elders). We will ask community leaders to identify around 30 men (ages 18-65) who are fathers, are seen as role models, and show a desire to learn. We will then reach out to these men, explain the program and training, and if they are interested, invite them to be interviewed. We will interview the interested men about previous formal counseling experiences, availability and interest in learning counseling and participating on a project, and ask them to complete a brief counseling role play. After interviewing interested men, around 20 men will be invited to a training. Having about 20 men at training will provide a large enough pool from which to choose 12 final counselors. This is based on previous pilot rates of interview to final counselor selection. After training, of the 20, 12 will be selected based on their performance in training measured with the ENACT Scale, a scale assessing core counseling competencies previously used in Eldoret; supervisors' assessment of their willingness to learn new material and openness to feedback; and knowledge of the intervention assessed with a written examine. **Training:** A 10-day training spread over weekends and afternoons, following piloted procedures, will focus on core clinical skills; specific session content; and emergency and safety planning. Training procedures are commensurate with other task-shifted LMIC interventions. Trainees will be compensated for their time. Supervisors, [name], and I will lead training. Training will be conducted in Kiswahili directly or through live translation. **Supervision:** Supervisors for peer-father counselors will be four local Kenyan individuals with bachelors' degrees in Psychology or in their final year of psychology training for their bachelors who are trained in LEAD. Local supervisors will consult weekly with [name] and myself. Supervision will use a tiered approach often used in task-shifted LMIC intervention delivery: 1) After a session, the supervisor debriefs with the counselor on immediate concerns (phone); 2) after listening to counselor sessions, supervisors consult with [name] and myself to solidify a supervision plan; 3) supervisors conduct supervision with counselors to plan the next session and practice skills.

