### Recruitment & Inclusion Exclusion Criteria:

We will work with **community leaders, peer-leaders supporting community substance use groups, and** existing Community Health Workers (CHWs) to recruit and identify eligible fathers with depression, any drinking, and a child at risk for MH problems (n=102 **Table 1**), one target child for each father and a co-caregiver (partner or relative who can report on family and child). *We will recruit to achieve balance in child age (50% 8-12, 50% 13-17).* All eligibility cut-off scores are based on validated measures. Inclusion includes the following: (1) Male between the ages of 18-65; (2) live with and be responsible for at least one child between the ages of 8 and 17 years of age; (3) screen positive for depression symptoms, operationalized as a score above 5 on the patient health questionnaire (PHQ-9); (4) Any reported alcohol use in the past 45 days measures with the AUDIT (score 1 or above); (5) child at risk of mental health issues as indicated by a score above 13 on the Strengths and Difficulties Questionnaire (SDQ) reported on by any caregiver; (6) willingness for co-caregiver and target child to participate in assessments (previously piloted strategy). Exclusion criteria includes: (1) Severe depression symptoms indicated a score above 19 on the PHQ-9; (2) Severe risk/likely alcohol dependence that warrants medical management indicated as a score 20 or above on the alcohol use disorder identification test (AUDIT); (3) Severe risk/likely substance use dependence that

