warrants medical management indicated as a ‘yes’ response in two or more questions in CAGE-AID; CAGE-AID is a standardized tool which is an adaption of the CAGE used for conjointly screening alcohol and drug dependence (Maina, Elizabeth & Wagoro, Miriam & Angeline, Kirui & Lincoln, Khasakhala.,2017). The CAGE-AID, as a screener, has shown validity as a screening tool for both alcohol dependence and drug dependence (Brown, R. L., & Rounds, L. A.,1995). The screener was originally adapted from the CAGE a standardized tool for measuring alcohol dependence whose acronym stands for ‘Cut down, Annoyed, Guilty, Eye opener’ (4) violent legal offenses (one question); (5) Indicators of severe violence at home assessed with key items from the Conflict Tactics Scale (CTS); (6) Inability to provide informed consent of complete procedures in Swahili or English; (7) serious mental illness (current or history); We use a low depression threshold for inclusion, given men often underreport symptoms; at this piloting stage, we will try to recruit men who have a child at risk for MH problems to explore how father treatment may influence child MH change (Aim 2). The youth does not have to be father’s biological child, just responsible for the care of the child and involved in the child’s life. The SDQ has shown sensitivity to change in Kenya.

**We will work with the on-site PI, study staff, and the MTRH community-based substance use group lead to identify community and peer leaders including CHWs. [Community leaders can consist of chiefs, village elders, religious leaders, or individuals well-connected in communities; individuals with formal and informal community positions, longstanding community knowledge, and can represent diverse sectors of the community. Peer-leaders are individuals with lived-experience who lead community-based substance use groups within Eldoret and surrounding communities.] We will approach leaders about the study to assess their interest in helping recruit fathers and peer-father counselors. If so, we will describe the type of fathers we hope to recruit using lay-terms based on inclusion and exclusion criteria. Leaders will then work with the trained consenters, Kenyan RA(s) and/or the PC who are all Kenyan psychologists, to reach out to potential participants, assess interest, and conduct eligibility screening and consent and assent procedures. Consenters will be trained to provide**

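### The target child is chosen by age before SDQ score with no minimum score, so the child followed need not be the at-risk child who qualified the family

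*Protocol*

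**What the plan says.** All of this is in the protocol, under Recruitment & Inclusion Exclusion Criteria.

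- **Who qualifies.** Criterion 2 asks that the father "live with and be responsible for at least one child between the ages of 8 and 17 years of age", so several children may be in range. Criterion 5 asks for a "child at risk of mental health issues as indicated by a score above 13" on the SDQ, from any caregiver's report. Table 1 repeats it as a father criterion: "Child at risk of MH problems (SDQ > 13".
- **Who is followed.** The study follows "one target child for each father and a co-caregiver". The paragraph after Table 1 gives the choice rule: "The target child will be chosen based on age first, then highest SDQ score based on caregiver screeners".
- **Age balance.** "We will recruit to achieve balance in child age (50% 8-12, 50% 13-17".
- **Why the SDQ criterion exists.** "we will try to recruit men who have a child at risk for MH problems to explore how father treatment may influence child MH change", with a pointer to Aim 2.
- **Wording of the criteria.** Criterion 5 speaks of a child. The term target child appears only in criterion 6: "willingness for co-caregiver and target child to participate in assessments".
- **The target child's own screen.** Under Consenting and Safety Considerations, the target child completes an SDQ once the father has been found eligible. No cut-off is attached to that score.

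**The concern.** Two rules act on the children of one family. The first, SDQ above 13, decides whether the family enters. The second, age and then SDQ rank, decides which child supplies the outcome data. The protocol does not tie the two to the same child, and the second rule puts the SDQ behind age with no floor.

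Take a father with a 10-year-old scoring 20 and a 15-year-old scoring 8 (an illustration, not a case in the protocol). The family meets criterion 5 through the younger child. If the older age band is the one that needs children, and age decides first, the 15-year-old is followed.

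The enrichment exists so that change in child mental health can be studied. Child SDQ is a secondary outcome in Table 2 and the end of the second and third pathways under Data Management and Analysis. A followed child who starts without elevated difficulties plausibly has less room to improve. Such a family could also look like one where only the father changed, which is one of the response patterns named in Aim 2.

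**Working it through.** The protocol states no figure that depends on the selection rule, so there is nothing to reproduce. The check has two parts: what the rule can mean, and how often it could select a child at or below 13.

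**1. Two readings of age first**

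- *Range reading.* Keep children aged 8-17, then take the highest SDQ. If the family qualified on a child in that range, the highest scorer is above 13. Share of followed children at or below 13: 0%.
- *Age-band reading.* Keep children in the band that the 50/50 balance needs, then take the highest SDQ within it. The qualifying child may be in the other band. The share can exceed 0%.

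The only age eligibility rule is 8-17, which favours the first reading. The 50/50 goal gives age a selecting role, which favours the second. No sentence decides between them.

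**2. Closed form for the age-band reading**

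Assume one child in each band, each scoring above 13 with probability p, independently, and a needed band unrelated to the scores.

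P(followed child at or below 13, given that at least one is above) = p(1−p) / [1−(1−p)²] = (1−p)/(2−p)

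- p = 0.3: 0.7/1.7 = 0.41
- p = 0.4: 0.6/1.6 = 0.375
- p = 0.5: 0.5/1.5 = 0.33

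If 30% to 50% of qualifying families have children in both bands (assumed), the overall share runs from 0.33 × 0.3 = 0.10 to 0.41 × 0.5 = 0.21.

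Independence is doubtful, because siblings share a household and raters. With p = 0.5 and a latent sibling correlation of 0.5 (assumed), both score above 13 with probability 1/3 and at least one with probability 2/3. The share is then (1/2 − 1/3)/(2/3) = 0.25 instead of 0.33.

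**3. Simulation with correlated siblings**

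Every input is assumed: one to three children aged 8-17 per family, ages uniform, SDQ mean 11, 13 or 15 with SD 5.5, sibling correlation 0.3 or 0.6, needed band drawn 50/50, and the other band used when the needed one is empty. Each scenario has 400,000 families. The share is taken among families with at least one child above 13.

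| Families with 1 / 2 / 3 children | Range reading | Age-band reading | Of 102 |
|---|---|---|---|
| 50% / 35% / 15% | 0% | 5.8% to 12.4% | 6 to 13 |
| 30% / 40% / 30% | 0% | 8.0% to 16.8% | 8 to 17 |
| 15% / 35% / 50% | 0% | 9.9% to 20.1% | 10 to 21 |

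Among families with two or more children in range, the age-band share is 10.4% to 22.1%. In one-child families the problem cannot arise.

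**4. What this does to the analysis**

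If a fraction f of followed children is at or below 13 in both arms, and those children gained nothing at all (an extreme assumption), the child contrast shrinks by the factor 1−f: 1 − 0.058 = 0.94 at the low end and 1 − 0.201 = 0.80 at the high end. Any gain in those children makes the shrinkage smaller. Of the roughly 75 families on which the Power paragraph bases the path model, 0.058 × 75 ≈ 4 to 0.201 × 75 ≈ 15 would have such a child.

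**The case against.** The strongest reply is that the rule may never be applied by age band. The 50/50 split is worded as a recruitment aim, and no sentence says that it is met by choosing among siblings. The surrounding text also treats the at-risk child and the followed child as one: the SDQ rationale speaks of the youth in the singular, and the co-caregiver is screened about the child. Following a low-scoring sibling would defeat the authors' own purpose.

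This stands in part. It shows what was probably intended, and it is why 0% belongs in the range. It does not settle the rule. Ranking by highest SDQ presupposes that several children are compared, the ordering puts age ahead of that ranking, and different consenters could apply it differently.

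Three stronger readings are tempting, and the protocol does not support them:

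- *That 10% to 20% of target children will be below the cut.* That figure needs assumed prevalence, assumed family structure, independent siblings and the age-band reading.
- *That the comparison of arms is biased.* The target child is chosen at screening and families are randomised, so below-cut children would be expected in both arms. The effect is dilution of a secondary outcome, in a pilot that says it is not powered for definitive estimates. Baseline SDQ is collected, so such children can be identified.
- *That the phrase about trying to recruit such men contradicts criterion 5.* It introduces a rationale; criterion 5 and Table 1 state the requirement. Aligning the wording is editorial.

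**Conclusion.** The point holds in a conditional form. As written, the rule allows a sibling at or below 13 to be followed in a family that qualified through another child, and nothing later in screening catches it. Whether this happens depends on what age first means, which the protocol leaves open.

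The size is 0% under the 8-17 reading. Under the age-band reading it is roughly 6% to 20% of target children, about 6 to 21 of 102, and that range rests wholly on the assumptions listed above. The loss is partial and confined to families with more than one child in range.

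A reader might infer that the at-risk enrichment fails outright or that the trial's main result is affected. Neither follows: the primary outcome is the father's PHQ-9, and the child contrast would be diluted, not biased. The point still deserves a change, because one natural reading of a stated selection order works against a stated purpose of the design.

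**What to change.** In the paragraph after Table 1, replace the selection sentence with a rule in three steps:

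1. The target child must be aged 8-17 and must personally have a caregiver-reported SDQ above 13.
2. Where more than one child meets this, the 8-12 / 13-17 balance decides among those children only.
3. If a choice remains, take the child with the highest SDQ.

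Use the term target child in criterion 5 and in the matching line of Table 1. As a tidy-up, bring the softer rationale sentence into line with the criterion.

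With this rule the share of followed children at or below 13 is 0% by construction. It needs no additional procedures. The cost is that the 50/50 age balance may be slightly harder to reach; the protocol gives no figures from which to say how much.

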## Treatment Conditions

**Intervention.** LEAD comprises behavioral activation (BA) and motivational interviewing (MI), as well as discussions of masculinity and a family focus throughout to target father's depression symptoms and

common comorbidities, such as drinking. LEAD is guided by a manual (in Swahili and English). It includes five, 60-90-minute weekly sessions. LEAD was adapted for context based on formative work. Each session begins with MH assessment and review of activity completion and ends with homework to monitor

activities. **Brief BA** has shown efficacy reducing depression symptoms as well as co-morbid alcohol and substance use across contexts and when delivered by lay-counselors. LEAD uses core BA components. **MI** (Session 1) has shown efficacy for increasing MH treatment engagement and reducing drinking behaviors, with strong effects when delivered by lay counselors. LEAD uses MI strategies to engage men in the treatment and increase commitment to addressing problems. MI strategies are then integrated throughout BA (Session 1-5) to enhance father motivation to complete activities as well as to build self-efficacy (e.g., when reviewing homework, counselors reflect successes).

**Waitlist Control (WL).** Those randomized to WL will complete assessments and be monitored at each timepoint; they will be offered LEAD following the last assessment. In a pilot, a control allows for a realistic examination of recruitment, randomization, implementation of LEAD, assessment procedures, and retention. If safety concerns arise, referrals and safety procedures will be implemented.

## Data Collection and Sampling and Power

We will compare LEAD to a monitored waitlist control (WL) on preliminary clinical and implementation outcomes. Using a random number generator in RStudio, we will randomize participants 2:1 to LEAD:WL, stratified by levels of drinking to ensure group exchangeability. Assessments will occur at baseline, immediately following LEAD, 1-month, and 3-month post-intervention. WL participants will be assessed at each timepoint; after the last assessment (~4.5 months), they will be offered LEAD.

Each father and his co-caregiver and designated child will complete assessments on family problems and MH at each timepoint (both arms); a procedure previously piloted. For fathers in LEAD, proximal mechanism outcomes will be assessed during LEAD (e.g., activity completion; Table 2). A subset of fathers, co-caregivers, and children in the LEAD arm will complete qualitative interviews 1 month after LEAD; peer-father counselors (N=12) and delivery stakeholders (supervisors, community leaders, MTRH personnel) will complete focus group

discussions and  
brief surveys 1-  
month post-LEAD.  
Trained Kenyan RAs  
will conduct  
assessments in

| Table 2. Aim 1 and Aim 2 Quantitative Measures |                                     |                                         |          |     |                     |
|------------------------------------------------|-------------------------------------|-----------------------------------------|----------|-----|---------------------|
| Outcome                                        | Construct                           | Measures*                               | Reporter | Aim | Alpha in Kenya      |
| Primary                                        | Depression Symptoms                 | PHQ-9                      | F        | 1   | .91                 |
| Secondary                                      | Drinking; Gender Norms              | AUDIT  ; GEM  | F        | 1   | .89; .56            |
|                                                | Disrupted Parenting +    | APQ                     | F, Co, C | 1   | F=.78, P=.85, C=.92 |
|                                                | Interparental Problems + | Togetherness Scale         | F, Co, C | 1   | F=.95, P=.96, C=.95 |
|                                                | Child Mental Health                 | SDQ                     | F, Co, C | 1   | F=.75, P=.75, C=.75 |
| Proximal Mechanism                             | Treatment Engagement                | Attendance                              | Tracked  | 2   | (% attended)        |
|                                                | Activity Completion +    | Homework Completion                     | PF, T    | 2   | (% complete)        |

|                                                                   |            |                                   |                          |       |   |                    |
|-------------------------------------------------------------------|------------|-----------------------------------|--------------------------|-------|---|--------------------|
| Swahili (with translation to English as needed) on secure tablets |            | Positive Reinforcement*           | Activity Emotion Valence | PF, T | 2 | (% + or -; yes/no) |
|                                                                   | Covariates | Age, Religion, Number of children |                          |       |   |                    |

**Notes:** F=father; Co=co-caregiver; C=child; PF=peer-father counselor; T=tracked; PHQ=Patient Health Questionnaire; AUDIT=Alcohol Use Disorder Identification Test; GEM=Gender-Equitable Men; APQ=Alabama Parenting Questionnaire; SDQ=Strengths & Difficulties Questionnaire; \*= Each measure transculturally translated, adapted, and tested in Kenya. += As per Figure 5, path 1 and 2 hypothesized mechanisms

with on-call access to a project psychologist/psychiatrist. Assessors will be blinded to condition.

Assessments will be conducted verbally unless a participant prefers otherwise. Participants will be compensated for travel and time.

**Power.** Anticipating loss to follow up of ~10% (seen in similar trials), power was calculated conservatively based on participation of 90 fathers randomized 2:1 (LEAD=60, WL=30). We will explore clinical change between groups to inform future testing. Based on the distribution of change in PHQ-9 scores observed in our proof-of-concept study, I will have 80% power to detect a moderate 0.60 to large > 1.00 effect size of continuous outcomes using a two-sided z-test, alpha level of 0.05. The sample also allows exploratory structural equation modeling of pathways (n=~75; 5 variables\*n=15). Across analyses, we are not powered to definitively estimate effects.

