### Specific Aims

**Aim 1. Explore the preliminary effectiveness of LEAD on father MH.** The *primary outcome* is father depressive symptoms assessed by the Patient Health Questionnaire, previously validated in Kenya. *Secondary outcomes* include fathers' drinking, father parenting, interparental problems, and child MH (ages 8-17) reported by the father, co-caregiver, and one child immediately and 1-month and 3-months post-LEAD.

**Aim 2. Use mixed methods to explore mechanisms driving change in father MH, father parenting, and child MH.** I will use structural equation modeling to explore clinical mediators between LEAD and father and child MH: LEAD → positive activities → father MH → parenting → child MH. To explore patterns of response/non-response, I will conduct qualitative interviews (fathers, co-caregivers, children, peer-counselors) on perceived change pathways and analyze LEAD-session transcripts of families showing different change outcomes (e.g., all changed, none, father MH only, child MH only). Qualitative data will be analyzed using the Framework Method. Data will be integrated to generate hypotheses and refinements.

**Aim 3. Explore feasibility and acceptability of implementing task-shifted MH treatment for fathers.** A mixed-methods process evaluation with fathers, peer-fathers, and delivery stakeholders will explore *implementation outcomes*: reach; retention; fidelity; feasibility; acceptability; and barriers to/facilitators of implementation, scale-up, and sustainability, including questions related to social determinants of health, e.g., gender norms, poverty, (interviews, focus groups, surveys).

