### Data Management and Analysis

Data will be collected on tablet that will be password protected and uploaded to a secure password protected server. No names will be collected on assessment materials (all deidentified). Sessions will be audio recorded on secure devices and delete once they are uploaded to the secure drive. Written materials such as consent and assent forms will be stored in a locked drawer in a locked office (See confidentiality for more details).

**Analysis.** (Aim 1) Quantitative longitudinal analysis will explore changes in depression and secondary outcomes from baseline to 3-month post-treatment based on intention-to-treat. Descriptive measures will be used to summarize data. Depression changes between baseline and post, 1-month post, and 3-month follow-up will be compared in the LEAD versus WL arms through mixed-effects linear regression models, with fixed effects for study condition, time, and the interaction between condition and time.

(Aim 2) Mixed-methods: quantitative and qualitative findings will be equally valued, analyzed separately, then integrated guided by hypothesized change pathways. **Quantitative:** we will explore pathways using structural equation modeling with data from Baseline, During Treatment [proximal mechanisms], Post, 1-month, and 3-month post. We will conduct a path analysis. We will explore 3 pathways: (1) the indirect effect of LEAD on father; (2) the direct and indirect effect of father depression on child MH via parenting, and (3) if we detect relationships in path 1 and 2, we will explore the direct and indirect effects of LEAD on child MH via father's depression. **Qualitative:** We will use the Framework Method with inductive and deductive coding. Two RAs will familiarize themselves with interview and session

transcripts. Next, they will open-code transcripts line-by-line, then deductively code transcripts. Once data are

coded, they will be charted and assessed with a framework matrix. Results will clarify and contextualize mechanisms, and potential moderators, to test in a future trial. (Aim 3) Table 3 shows measures for Aim 3.

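### Aim 2, path 1: activity completion is recorded only in the LEAD arm, so an indirect effect of LEAD through it is not identified

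*Protocol*

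**What the plan says.** Protocol, Specific Aims, sets the Aim 2 model as the chain "LEAD → positive activities → father MH → parenting → child MH". Data Management and Analysis lists three paths: LEAD's indirect effect on the father; father depression to child mental health, directly and through parenting; and a third that is conditional, "3) if we detect relationships in path 1 and 2, we will explore the direct and indirect effects of LEAD on child MH", by way of the father's depression. The proximal mechanisms recorded during treatment are among the data for the model.

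Data Collection and Sampling and Power says who has those data: "For fathers in LEAD, proximal mechanism outcomes will be assessed during LEAD (e.g., activity completion; Table 2". Table 2 measures activity completion as "Homework Completion", from the peer-father counselor or tracking, and marks it as a hypothesised mechanism for paths 1 and 2. Treatment Conditions shows where it comes from: counselors review activities at the start of each LEAD session and set homework at the end. Waitlist fathers are offered LEAD only after the last assessment, at about 4.5 months. What both arms share is narrower: each father, co-caregiver and child "will complete assessments on family problems and MH at each timepoint (both arms".

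On sample size, the Power paragraph says "The sample also allows exploratory structural equation modeling of pathways" and gives about 75, as 5 variables times 15.

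**The concern.** An indirect effect of LEAD needs a contrast between arms in the mediator. As measured, the mediator does not exist for waitlist fathers, so path 1 has no such contrast. What can be computed is whether LEAD fathers who did more homework improved more. Fathers who are more motivated or less depressed may do more homework and also improve more, so that association is not evidence that LEAD works through activities. The protocol says Aim 2 results will clarify mechanisms to test in a future trial, and Study Implications says they can guide refinement of the treatment. An adherence correlation reported as mediation would misdirect both. In addition, path 3 can be estimated from both arms, yet it is made conditional on detecting path 1.

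**Working it through.** **Inputs from the protocol.** 102 fathers enrolled, randomised 2:1; 90 assumed analysed (60 LEAD, 30 waitlist); model sample 5 × 15; mediator recorded in LEAD only.

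**1. The plan's own figure.** 5 × 15 = 75. It reproduces, and lies below the 90 expected in both arms together.

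**2. Who has the mediator.** LEAD enrolled: 102 × 2/3 = 68. LEAD analysed: 90 × 2/3 = 60. Waitlist: none.

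**3. Identification.** Write the indirect effect as a × b, where a = mean(M | LEAD) − mean(M | waitlist) and b is the slope of outcome on M given arm. The second mean in a is not observed. In LEAD fathers alone, the columns [1, LEAD, M] have rank 2 of 3, because the LEAD column equals the constant. Neither a nor the direct effect of LEAD is identified, and more fathers would not change that.

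**4. Waitlist coded 0 (not stated in the protocol).** Now a = mean(M | LEAD). M does not vary in the waitlist, so b is exactly the within-LEAD slope, r·s_Y/s_M, and

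- indirect = mean(M)·r·s_Y/s_M
- direct = (difference in arm means) − indirect

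The waitlist informs the total effect but adds nothing to b.

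**5. Size under assumed inputs.** Nothing here except the 60:30 split and the 0.60 effect size comes from the protocol. Let completion be 0.60 + 0.15u + 0.15e, kept between 0 and 1, where u is an unmeasured cause and e is noise. Let the outcome have SD 1 within arm and loading −0.4 on u. The total LEAD effect is −0.60 SD, and completion has no effect at all.

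- s_M = √(0.15² + 0.15²) = 0.212
- r = −0.4 × 0.15 / 0.212 = −0.283
- indirect = 0.60 × (−0.283) / 0.212 = −0.80
- direct = −0.60 + 0.80 = +0.20

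A simulation of 4,000 trials gave −0.81 and +0.20, with an arm–mediator correlation of 0.86 (VIF about 3.9). The true mediated effect is zero, yet the fit attributes more than the whole benefit to mediation.

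Range over mean completion m and SD s (both assumed), holding r at −0.283. With a 2:1 split, R² = (2/9)m² / [(2/9)m² + (2/3)s²], VIF = 1/(1 − R²), and indirect = (m/s)·r. For m = 0.7, s = 0.25: R² = 0.109/(0.109 + 0.042) = 0.72.

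| m | s | m/s | arm–mediator correlation | VIF | spurious indirect (SD) |
|---|---|---|---|---|---|
| 0.6 | 0.30 | 2.0 | 0.76 | 2.3 | −0.57 |
| 0.7 | 0.25 | 2.8 | 0.85 | 3.6 | −0.79 |
| 0.8 | 0.20 | 4.0 | 0.92 | 6.3 | −1.13 |

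The spurious effect is proportional to r, and vanishes if engagement is unrelated to outcome for any other reason.

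**6. The other paths.** Father depression (PHQ-9), parenting (APQ) and child mental health (SDQ) are measured in both arms at every timepoint. Paths 2 and 3 can be fitted on about 90 families.

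**The case against.** **It can be computed.** A waitlist father does no LEAD homework, so zero is arguably his true value. That stands as far as fitting goes. But a is then only mean homework completion, and b is only the within-LEAD slope.

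**Every mediation analysis has a non-randomised mediator–outcome slope.** True, and it would remain under either repair below. With a measure taken in both arms, however, the first link becomes a randomised contrast, which path 1 now lacks.

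**Aim 2 is exploratory, not powered, and gives qualitative evidence equal weight.** This stands and lowers the severity. It excuses imprecision but not non-identification.

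**The analysis plan can settle it.** It could say how waitlist fathers enter the model. It cannot supply a measure never collected from them.

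**Path 1 may use another mediator.** Figure 5, which the Table 2 notes cite for these paths, is not in the text reviewed. Specific Aims nevertheless names positive activities as the first link. Attendance, listed under "Treatment Engagement", carries no mechanism mark, and the mark on positive reinforcement ("Activity Emotion Valence") is unclear in the text as read. The point therefore rests on activity completion alone.

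**Conclusion.** Path 1 is wrong as written. With activity completion recorded only in LEAD, no effect of LEAD through it is identified. With zeros for the waitlist, the result is an adherence association among about 60 to 68 fathers. The −0.81 SD illustration and the −0.57 to −1.13 range depend on assumed inputs; the identification argument does not. Severity is moderate, because Aim 2 is exploratory and the primary Aim 1 analysis is unaffected.

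A reader might infer more, but the protocol does not support it:

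- **That the sample of 75 is itself an error because only 60 fathers have the mediator.** In a LEAD-only fit the arm variable drops out, leaving 4 × 15 = 60, and with both arms 90 exceeds 75. The defect is identification, not sample size.
- **That the father-to-child path would be discarded.** That is path 2, which is not conditional on anything. Only path 3 is.
- **That low power would usually close the condition on path 3.** The protocol sets no significance level for detection, and the power of a two-group comparison of means is not the power of path 1 or path 2.

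**What to change.** Choose one of two changes.

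**(a) Relabel.** Describe path 1 as a within-LEAD association of activity completion with outcome, with its own n (about 60 to 68) and no mediation claim. Start the randomised mediation model at the father's PHQ-9, using both arms: LEAD → PHQ-9 → parenting → child SDQ, about 90 families. The cost is protocol wording only.

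**(b) Measure in both arms.** Ask the same brief positive-activity questions of LEAD and waitlist fathers at the existing research-assistant assessments, and use those answers as the mediator. The cost is a few more questions at visits that already take place. This option is lost for any waitlist father whose assessments are already complete.

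Under either option, remove the dependence of path 3 on detecting path 1 as now specified, since path 3 uses only variables measured in both arms. Path 2 needs no change.
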